## Abstract

**Introduction::**

Coronary microvascular disease (CMVD) can affect the structure, function, and metabolism of the heart, and has an important impact on the occurrence, development and prognosis of coronary artery disease (CAD). Shexiang Tongxin dropping pill (STDP) can dilate blood vessels, alleviate inflammation, reduce endothelial damage, and improve coronary microvascular function in mice with myocardial infarction. This study aims to assess the impact of STDP on stable coronary artery disease (SCAD) patients with normal FFR and CMVD.

**Methods and analysis::**

This is a single-center, prospective randomized trial that will enroll 64 SCAD patients, CAD with normal FFR and CMVD. Patients will be randomly divided into study group and control group in a 1:1 fashion. On the basis of conventional drug treatment, the former will receive STDP while the latter will not. The follow-up period of the subjects is 12 months, and clinical follow-up will be conducted before discharge, 30 days, 3 months, 6 months, and 12 months after procedure to complete the detection of relevant indicators. The primary endpoint is the change of index of microcirculatory resistance (ΔIMR) at 12-month follow-up.

**Discussion::**

The present study will be the first randomized control study to evaluate the efficacy and safety of STDP on SCAD patients, CAD with normal FFR and CMVD, which will provide a broader idea and more experimental basis for improving the treatment of CMVD.

**Trial registration::**

This is a protocol for the randomized clinical trial which has been registered in the Chinese clinical Trial Registry with an identifier: ChiCTR2000032429.

## Introduction

1

Coronary artery disease (CAD) is a common atherosclerotic cardiovascular disease that seriously harms human health. Among them, in some patients with CAD, the symptoms are caused by localized narrowing of the epicardial coronary arteries, which can be alleviated by drug therapy and revascularization if necessary. However, there is still a considerable part of patients with CAD, whose fractional flow reserve (FFR) test is normal but evidence of myocardial ischemia still exist, which may be associated with coronary microvascular disease (CMVD).

CMVD refers to the clinical syndrome of objective evidence of exertional angina or myocardial ischemia caused by abnormal structure and/or function of coronary prearterioles and arterioles under the action of various pathogenic factors.^[1]^ Ample evidence has revealed that microvascular structure changes or remodeling have been related to CMVD. Meanwhile, endothelial dysfunction in resistance coronary vessels is an extremely important contributor to CMVD.^[2]^ The WISE study included female patients with normal coronary angiography and reduced coronary flow reserve (CFR) and found that the incidence of cardiac death, stroke, and heart failure increased by 24% after 5 years.^[3]^ Spoladore found that changes in coronary microvascular blood flow, especially coronary endothelial dysfunction was the main cause of impaired cardiac function.^[4]^ Therefore, timely diagnosis and treatment of CMVD will effectively improve the symptoms and prognosis of the patients.

After study for over 20 years, the invasive and non-invasive assessment of coronary microvascular function has been established. Because of lack of regional perfusion abnormalities typically seen in obstructive CAD, traditional non-invasive ischemia tests may be normal in patients with CMVD.^[5]^ It is thought that cardiac magnetic resonance (CMR) imaging holds most promise as the first choice for noninvasive imaging.^[5]^ Invasive tests including CFR and index of microcirculatory resistance (IMR) are the reference standard for the diagnosis of CMVD. IMR is an index to evaluate the function of distal microvessel in patients with coronary artery stenosis, characterized by high specificity and good repeatability.^[6]^ Value of IMR ≥ 25 units is indicative of abnormal microcirulatory function.^[7]^

The treatment of CMVD has so far been empirical based on traditional therapies for CAD and the curative effect is not evident. The application of traditional Chinese medicine has opened up new ideas for us. Shexiang Tongxin dropping pill (STDP) is a traditional China Food and Drug Administration (CFDA)-approved prescription medicine (approval no. Z20080018), based on the ancient prescriptions “Zhi Bao Dan” and “Liu Shen Pills,” which consists of a combination of seven valuable drugs such as artificial musk, secretio bufonis, total saponins of ginseng, salvia miltiorrhiza, artificial bezoar, bear gall, borneol, etc. Studies have shown that STDP can increase the expression of endogenous nitric oxide synthase (eNOS) gene, increase the content of NO in plasma, and thus play a role in vasodilating, inhibiting platelet aggregation, scavenging oxygen free radicals so as to improve microcirculation dysfunction.

However, there is no clinical study to observe and confirm whether STDP can improve the microvascular function of patients with CAD. Thus, a prospective randomized controlled trial will be designed to address the issue. We will test the hypothesis that STDP can significantly improve the coronary microvascular function in stable CAD (SCAD) patients with normal FFR and CMVD. In this article, we describe the study design discuss the rationale for the specific approaches employed.

## Methods and analysis

2

### Study design

2.1

This is a single-center, prospective randomized trial that will enroll 64 SCAD patients with normal FFR and CMVD. The protocol has been approved by the Ethics Committee of Sir Run Run Show Hospital Affiliated to Zhejiang University School of Medicine (No.20200423–36). Participants who meet the eligibility criteria will be enrolled and randomly allocated to study group and control group in a 1:1 fashion. On the basis of conventional drug treatment, the former will receive STDP while the latter will not. The follow-up period of the subjects was 12 months, and clinical follow-up will be conducted before discharge, 30 days, 3 months, 6 months, and 12 months after procedure to complete the detection of relevant indicators. The study flow chart is shown in Figure 1.

**Figure 1 F1:**
[figure not shown]
Study flow chart.

Corresponding parameters shown in Table 1 including laboratory tests and other indicators will be recorded or assessed at each follow-up by the responsible physician.

**Table 1 T1:**
[figure not shown]
Planned visits and parameters.

### Hypothesis

2.2

This study hypothesizes that for SCAD patients with normal FFR and CMVD, the addition of STDP based on the conventional drug treatment in the study group can significantly improve the coronary microvascular function compared with the control group (the key index is IMR).

### Participant

2.3

We will enroll patients aged 18 to 80 years and the major clinical inclusion and exclusion criteria are listed in Table 2. In addition, for patients who meet clinical criteria, coronary angiography will be further performed. The inclusion criteria for the lesions are as follows: Coronary angiography shows diameter stenosis ≥50% in at least one of the three main coronary arteries with FFR ≥ 0.80. No need for revascularization (including balloon inflation, stent implantation, coronary artery bypass grafting, etc), IMR ≥ 25. At the same time, the following lesions need to be excluded:

Thrombotic lesions;Coronary spasm without significant stenosis;Left main disease with a diameter stenosis rate of ≥50%;Type C-F dissection of coronary artery.

**Table 2 T2:**
[figure not shown]
Clinical inclusion and exclusion criteria.

### Recruitment

2.4

The study was carried out at Sir Run Run Show Hospital Affiliated to Zhejiang University School of Medicine. The patients interested in participating in the study will be evaluated by clinicians to determine their qualifications. Participants must give written informed consent which should be acquired after sufficient and detailed explanation to research situation (including confidentiality, risk and benefits, purpose of the study, etc).

### Randomization

2.5

A computer-generated randomization schedule was prepared prior to recruitment by a statistician not otherwise involved in the trial, using stata 11 to implement a random number sequence according to simple randomization with a 1:1 allocation ratio. Group assignments were concealed in opaque sequentially numbered envelopes according to the randomization schedule. A print copy of the randomization schedule was stored in a sealed envelope under at research office. With a similar rate of recruitment over time into the two intervention groups, either randomization sequence would be expected to produce balanced intervention groups.

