### Sample size

2.8

The sample size is calculated according to the main evaluation index ΔIMR at 12-month follow-up. Based on previous study, the level of ΔIMR is hypothesized to be 15.0 ± 6.0 and 10.0 ± 4.0 in study group and control group, respectively. When the calculation is performed using 90% power, and a 5% significance level (one-sided test), random distribution ratio is 1:1, the minimum number of members in each group is 25. Considering a drop-out rate of 20%, the needed sample size is approximately 32 participants for each group. Therefore, a total of 64 participants are needed for the present study.

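### Simple randomisation of 64 patients gives balanced arms only on average: a 27/37 or worse split has a 26% chance, though the cost is small

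*Protocol article*

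**What the plan says.** Section 2.5 (Randomization) of the protocol article describes a computer-generated schedule prepared before recruitment, "using stata 11 to implement a random number sequence according to simple randomization with a 1:1 allocation ratio". It names no blocks or strata. The section ends: "With a similar rate of recruitment over time into the two intervention groups, either randomization sequence would be expected to produce balanced intervention groups."

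Section 2.8 (Sample size) states that "the minimum number of members in each group is 25" and that, after 20% drop-out, "the needed sample size is approximately 32 participants for each group", 64 in total. The planning values are that "the level of ΔIMR is hypothesized to be 15.0 ± 6.0 and 10.0 ± 4.0 in study group and control group, respectively", with 90% power and a one-sided 5% test.

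Section 2.9.3 (Efficacy analysis) refers comparisons between groups back to section 2.9.2, which names a group t test for normal data and a Wilcoxon rank sum test otherwise. Neither section mentions adjustment for baseline.

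**The concern.** Simple randomisation equalises arm sizes in expectation. In a trial of 64 it leaves an appreciable chance of clearly unequal arms.

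The reason given for expecting balance does not help. How fast each arm fills follows from the allocation sequence, so a similar rate of recruitment into both arms is balance restated, not a mechanism that produces it. The wording is also loose: the sentence refers to either of two sequences, while the section describes one schedule.

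Two things could be at stake. Unequal arms can lower power. If the t test pools variances, unequal arms combined with the unequal SDs of section 2.8 (6 and 4) also move the type I error away from 5%.

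**Working it through.** **Inputs.** N = 64, 1:1 allocation, about 32 per arm, drop-out 20%, difference 15.0 − 10.0 = 5.0, SDs 6.0 (study) and 4.0 (control), one-sided α = 0.05, power 90% (section 2.8). Simple randomisation (section 2.5) is read as independent draws with probability 0.5.

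**Reproducing the plan's figures.** 25/0.80 = 31.25, rounded up to 32 per arm and 64 in total, as stated. The 25 follows from an SD of 6 in both arms: 2 × [6 × (1.645 + 1.282)/5]² = 24.7, so 25. With both stated SDs, (36 + 16) × (1.645 + 1.282)²/25 = 17.8, so 18 per arm, or 19 with the t distribution.

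**Distribution of the split.** The study-arm size X follows Binomial(64, 0.5).

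- P(X = 32) = C(64,32)/2^64 = 9.9%
- P(27/37 or worse) = 2 × P(X ≤ 27) = 2 × 0.130 = 26.0%
- P(24/40 or worse) = 2 × P(X ≤ 24) = 6.0%

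The last two count both directions. The chance that one named arm is the one with 27 or fewer is 13.0%.

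**Power after 20% loss in each arm.** Welch test, SE = √(36/n₁ + 16/n₂), noncentrality 5/SE, one-sided 5%.

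| Randomised (study/control) | Evaluable | SE | 5/SE | Power |
|---|---|---|---|---|
| 32/32 | 25.6/25.6 | 1.425 | 3.51 | 96.5% |
| 27/37 | 21.6/29.6 | 1.486 | 3.37 | 95.1% |
| 37/27 | 29.6/21.6 | 1.399 | 3.57 | 97.0% |
| 24/40 | 19.2/32.0 | 1.541 | 3.24 | 93.6% |
| 40/24 | 32.0/19.2 | 1.399 | 3.57 | 97.0% |

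Weighted over all splits by their binomial probabilities, power is 96.2%. Power exceeds the 32/32 value when the study arm, with the larger SD, is the larger one.

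**Type I error, if the group t test is pooled.** Take 22/29 evaluable, roughly a 27/37 split after 20% loss. By simulation the error is about 6.2% when the smaller arm has SD 6 and about 4.0% when it has SD 4. Two-sided the figures are 6.3% and 3.9%; one-sided they lie slightly closer to 5%. At 25/25 the error is about 5%. Averaged over all splits it is about 5.1%.

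**The case against.** The strongest reply is that the article promises very little. It speaks of balance as expected, and of approximately 32 per arm. Simple 1:1 randomisation does give equal arms in expectation, is valid, and yields the least predictable allocation. That last property has value in a single-centre trial whose control group receives no STDP and for which no placebo is described. Power stays above the 90% target at 24/40. The shifts in type I error are conditional on one split, go in opposite directions, and presuppose a pooled test that section 2.9.2 does not name.

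All of this stands, and it limits the point to a minor one. It does not rescue the closing sentence of section 2.5, because the recruitment condition does not secure balance.

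A reader might infer more than the document supports:

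- *That exactly 32/32 was promised, so the 9.9% refutes the plan.* No section promises it.
- *That any unequal split defeats the minimum of 25 evaluable per arm.* An arm of 31 does give 31 × 0.8 = 24.8 on average. But the 25 rests on an SD of 6 in both arms; with the stated SDs about 19 per arm give 90% one-sided power.
- *That power falls to 88%.* That is the two-sided figure at 24 study/40 control. The stated test is one-sided.
- *That arms drift apart over calendar time as care or operators change.* The article reports no such change.
- *That baseline IMR becomes materially less balanced.* The expected value of 1/n₁ + 1/n₂ rises by only about 1.6% over 32/32.

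**Conclusion.** The point holds as a minor design improvement. Section 2.5 asserts balance from a method that gives it only on average, for a reason that does not support it, and a split of 27/37 or worse has a 26% chance. On the plan's own inputs the average cost is 96.5% − 96.2% = 0.3 percentage points of one-sided power. The average type I error of a pooled test is close to nominal, and only the error conditional on an unequal split moves noticeably. Neither the validity of the trial nor its stated power is threatened.

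This rests on independent 50:50 draws for exactly 64 patients, 20% loss in both arms, the SDs of section 2.8, and, for the type I error only, a pooled t test. If the list was in fact constrained to 32/32, the figures do not apply, but section 2.5 then names the wrong method and still needs correcting.

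**What to change.** **If the list is not yet in use:** have the same independent statistician generate it with permuted blocks of randomly varying size, for example 4 and 6, with the sizes withheld from recruiting staff. An unfinished block of 6 leaves the arms at most 3 patients apart. The cost is one new list and slightly more predictable allocation where treatment is not masked; varying and concealing the block sizes limits this.

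**If the list is in use:** keep it. Since section 2.5 says the schedule was prepared before recruitment, this may be the case that applies. Reword the closing sentence to say that arm sizes are expected to be equal only on average, and remove the recruitment condition and the reference to either sequence. Then, in place of the unadjusted group t test, compare 12-month ΔIMR between arms with adjustment for baseline IMR, using a variance estimate valid for unequal arm sizes and SDs. Eligibility requires an IMR measurement (section 2.3), so every patient has the covariate and no new data are needed. The cost is a change of text, to be made before outcome data are compared by arm.

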### Intervention

2.6

The study group should be given routine medical treatment for SCAD (including but not limited to anti-platelet aggregation (such as aspirin, once daily, 0.1 g each time), lipid-regulating (such as atorvastatin, once daily, 20 mg each time) and other drugs), and on this basis, add STDP orally, three times a day, 70 mg each time; By contrast, the control group should be given routine medical treatment for SCAD (including but not limited to anti-platelet aggregation, lipid-regulating and other drugs).

### Endpoints

2.7

#### Primary and secondary endpoints

2.7.1

The primary endpoint is the change of Index of Microcirculatory Resistance (ΔIMR) at 12-month follow-up. The secondary endpoints are major adverse cardiovascular events (MACE, including cardiac death, myocardial infarction, ischemic stroke, unstable angina requiring hospitalization, coronary revascularization) at 12-month follow-up; the change in corrected TIMI frame count (ΔCTFC) after 1-year follow-up; the change in coronary flow reserve (ΔCFR) at 1-year follow-up.

#### Safety endpoints

2.7.2

All parameters related to the participants’ safety including vital signs, physical examination, hematologic test, biochemical test, and judged cardiovascular events will be documented on the CRF at every visit. Any adverse events (AEs) that occur after taking test drug, regardless of the severity and whether they are related to the test drug, will be documented on the CRF and reported in a timely manner. If the AE is severe and related to STDP, the participant will be withdrawn from the study, and the follow-up and appropriate treatment will be provided to them.

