#### Safety evaluation

2.9.4

According to the study group and the control group, the number and proportion of abnormal cases before and after treatment are described respectively. AEs are described by the number and incidence of AEs, and the proportion is tested by continuous correction χ^2^ test or Fisher's exact probability method. At the same time, depict the specific manifestations, degree and relationship with the study drug of all AEs occurred in each group of cases in detail.

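### The adverse event recording rule starts at intake of a drug that controls never take, and so conflicts with the planned between-group comparison of adverse events

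*Protocol article*

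**What the plan says.** Four places in the protocol article bear on this.

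- **Section 2.7.2 (Safety endpoints)** has two recording statements. The first covers vital signs, physical examination, blood tests and cardiovascular events, and is not limited by arm: "judged cardiovascular events will be documented on the CRF at every visit". The second is the only rule for AEs in general, and it starts at drug intake: "Any adverse events (AEs) that occur after taking test drug", whatever their severity or relation to the drug. The following sentence, on related severe events, names STDP, so the test drug is STDP.
- **Section 2.1 (Study design)** describes the two groups: "the former will receive STDP while the latter will not".
- **Section 2.6 (Intervention)** gives the comparator: "By contrast, the control group should be given routine medical treatment for SCAD". The article describes neither a placebo nor blinding.
- **Section 2.9.4 (Safety evaluation)** sets the analysis: "AEs are described by the number and incidence of AEs", and "the proportion is tested by continuous correction" chi-square or Fisher's exact method. It also asks for the manifestations, degree and "relationship with the study drug of all AEs occurred in each group of cases in detail".

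No section states one AE window that applies to both groups.

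**The concern.** The analysis needs control-arm AEs that the recording rule, as worded, does not cover. Site staff complete case report forms from the recording rule, not from the statistics section. A rule that names the drug also invites closer questioning of the patients who take it, all the more where controls take nothing in its place.

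What is at stake is the comparison of AEs other than the visit-based safety data and cardiovascular events, for example gastrointestinal complaints or rash. If these are sought less in controls, ordinary background complaints will look like an excess on STDP. Safety is a stated aim alongside efficacy, and unequal ascertainment cannot be repaired once the data are in.

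**Working it through.** **1. Is there a conflict in the text?**

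| Question | Section | Answer |
|---|---|---|
| When does AE recording start? | 2.7.2 | After taking the test drug |
| Do controls take it, or a placebo? | 2.1, 2.6 | No STDP; no placebo described |
| Are control AEs analysed? | 2.9.4 | Yes: described in each group, and proportions tested |
| Is anything recorded regardless of arm? | 2.7.2 | Yes: vital signs, examination, blood tests, judged cardiovascular events |
| Is a common AE window stated? | none | No |

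Read literally, the rule leaves controls with no recordable AE outside the items in the fourth row. Section 2.9.4 assumes that they have some. The two cannot both be followed as worded. Section 2.9.4 also asks for relationship to the study drug in each group, a judgement that has no meaning for controls.

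**2. How much could it matter?**

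The article gives no AE rate and no AE power, so there is no figure of its own to reproduce. What follows is an illustration.

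Inputs:
- 32 per arm: 64 participants at 1:1 (section 2.8), with drop-out ignored.
- Test: Fisher's exact, one of the two named in section 2.9.4.
- *Assumed:* two-sided level 0.05.
- *Assumed:* true AE risk p equal in both arms, 20% to 30% as the main range and 10% to 40% as the wider one.
- *Assumed:* fraction c of control AEs captured, with c = 1, 0.5 or 0.

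Recorded AE counts are A ~ Bin(32, p) on STDP and B ~ Bin(32, c·p) in controls. The false-signal probability is the sum of P(A = a)·P(B = b) over all tables (a, b) with Fisher p < 0.05.

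For c = 0 this can be followed by hand, because B is always 0:
- 5/32 versus 0/32 gives Fisher p = 0.053, not significant.
- 6/32 versus 0/32 gives 2·C(32,6)/C(64,6) = 2 × 906,192 / 74,974,368 = 0.024, significant.
- The false-signal probability is therefore P(A ≥ 6). It is 0.640 at p = 20% (expected count 32 × 0.20 = 6.4) and 0.949 at p = 30% (expected count 32 × 0.30 = 9.6).

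All cases:

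| True AE risk, both arms | Equal capture (c = 1) | Half capture (c = 0.5) | No capture (c = 0) |
|---|---|---|---|
| 10% | 1.1% | 2.3% | 9.4% |
| 20% | 2.4% | 10.9% | 64.0% |
| 30% | 2.8% | 21.5% | 94.9% |
| 40% | 3.0% | 32.9% | 99.7% |

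The continuity-corrected chi-square gives nearly the same: at 20% and 30%, 2.3% and 2.4% with equal capture, 10.9% and 20.3% with half capture, and 64.0% and 94.9% with none.

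Relative to equal capture, half capture multiplies the false-signal rate by 10.9/2.4 ≈ 4.5 at 20% and by 21.5/2.8 ≈ 7.7 at 30%. At 10% the absolute effect is small.

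**The case against.** The strongest reply is that section 2.9.4 shows what the authors intend. It organises safety by study and control group and asks for every AE in each group, which would be pointless if controls could have none. On this view the sentence in section 2.7.2 is only loosely worded. **This stands as evidence of intent.** It does not remove the conflict, because the only AE recording rule in the article still says something else.

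A reader might infer more than the documents support:

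- *That AEs are defined so as to exclude controls, and the comparison is biased as written.* The sentence is a recording rule, not a definition, and section 2.9.4 points the other way. Bias depends on how the rule is applied.
- *That everything except laboratory data is collected on STDP only.* Physical examination, vital signs and judged cardiovascular events are also recorded at every visit without limit by arm, and the list is not presented as exhaustive.
- *That coronary background events would appear as harm from STDP.* Cardiac death, myocardial infarction, ischaemic stroke, hospitalised unstable angina and revascularisation form the MACE endpoint, which is compared between groups (sections 2.7.1 and 2.9.3).
- *That events between randomisation and first dose are lost.* The article states no such interval, and counting from first intake is a common convention within a treated arm.
- *That 6/32 versus 0/32 is what to expect.* It needs both an assumed AE rate and zero capture in controls, which runs against section 2.9.4. It is the worst case.

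A further objection is that the full protocol, the visit table and the case report form are not shown and may set out AE questioning in both arms. They may, and their silence here is not the complaint. The point rests on a rule that the article does state and that does not fit a trial in which controls take no test drug.

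**Conclusion.** The point holds as a conflict between the recording rule in section 2.7.2 and the analysis in section 2.9.4. If the rule is followed literally, or controls are questioned less actively, AEs outside the visit-based safety data and cardiovascular events will be under-counted in controls, and the AE comparison will be biased against STDP.

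At an equal true risk of 20% to 30%, partial under-capture is the more plausible case and raises the false-signal rate from about 2–3% to about 11–21%. Zero capture, at 64–95%, is the upper bound. These figures rest on assumed AE rates, an assumed two-sided 5% level, assumed capture fractions and 32 analysed per arm. The textual conflict rests on none of them.

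Severity: should be fixed. Change in IMR, MACE, the changes in CTFC and CFR, and the laboratory safety data are not affected.

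**What to change.** Replace the opening of the AE rule in section 2.7.2 with a statement that applies to both arms, for example: *All AEs from randomisation to the 12-month visit are elicited and recorded in both groups, at the same visits and with the same questions.*

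In section 2.9.4, state that relatedness to STDP is assessed in the study group only, and that all-cause AE incidence is compared by randomised group.

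If the full protocol or case report form already works this way, the article's wording only needs to be brought into line. Otherwise the cost is a short amendment and an instruction on the form. Both groups already share one visit schedule (section 2.1), so no extra visits are needed, and no treatment or clinical management rule changes.

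### The safety section withdraws participants with a severe STDP-related AE from the study, a rule only the STDP arm can trigger, so 12-month outcomes risk being lost in one arm

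*Protocol article*

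**What the plan says.** Section 2.7.2 (Safety endpoints) sets a mandatory rule: "If the AE is severe and related to STDP, the participant will be withdrawn from the study". The sentence then continues: "and the follow-up and appropriate treatment will be provided to them". It does not say what that follow-up contains.

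Section 2.1 (Study design) gives STDP to one arm only: "On the basis of conventional drug treatment, the former will receive STDP while the latter will not". Section 2.6 (Intervention) confirms that controls have routine treatment and mentions no placebo.

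Section 2.7.1 fixes the main outcome at a single late time point: "The primary endpoint is the change of Index of Microcirculatory Resistance (ΔIMR) at 12-month follow-up". MACE, CTFC and CFR are also assessed at 12 months. The Introduction classes IMR and CFR as invasive: "Invasive tests including CFR and index of microcirculatory resistance (IMR) are the reference standard for the diagnosis of CMVD".

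Section 2.8 (Sample size) assumes that "the level of ΔIMR is hypothesized to be 15.0 ± 6.0 and 10.0 ± 4.0 in study group and control group, respectively", and allows for losses with one rate for both arms: "Considering a drop-out rate of 20%, the needed sample size is approximately 32 participants for each group".

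**The concern.** Two decisions are merged in one sentence: whether a participant goes on taking STDP, and whether that participant remains in the trial. The first is clinical. The second determines whether the randomised comparison can still be made.

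The trigger needs an event judged related to STDP, and no control can have one. A control with an equally severe event stays in, so any loss caused by this rule falls on one arm. The primary outcome is a repeat invasive measurement at 12 months, obtained only if the participant is deliberately brought back. If withdrawal means that this does not happen, no later analysis plan can recover the value. Should those lost also differ in outcome from the rest of their arm, a comparison of the participants who remain no longer estimates the effect in everyone randomised. Later MACE in the STDP arm could be lost in the same way.

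The 20% drop-out allowance protects the number of evaluable participants. It does not protect the comparability of the arms.

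**Working it through.** **Inputs from the protocol article.** ΔIMR 15.0 (SD 6.0) with STDP and 10.0 (SD 4.0) in control, so a planned difference of 5.0; one-sided 5% level; 90% power; 25 evaluable and 32 randomised per arm (section 2.8). The larger value is taken as the better outcome, as the hypothesis implies.

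**Assumptions, not in the documents.** The share of the STDP arm withdrawn under this rule (w), and the mean ΔIMR those participants would have shown (m). All results below apply only if their 12-month IMR is not collected and completers are compared.

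**1. The plan's own figure.** With SD 6 in both arms, n = 2 × (1.645 + 1.282)² × 6² / 5² = 24.7, so 25 per arm. Then 25 / (1 − 0.20) = 31.25, so 32 per arm and 64 in total. The stated sample size reproduces and is not in dispute.

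**2. Withdrawn participants show the control change.** Those who stay on STDP average 15 and the withdrawn average m = 10. The as-randomised difference is 5 × (1 − w), while completers show 15 − 10 = 5.

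| Withdrawn from STDP arm | As randomised | Completers | Ratio |
|---|---|---|---|
| 1 of 32 | 5 × 31/32 = 4.84 | 5.0 | 1.03 |
| 10% (about 3 of 32) | 4.50 | 5.0 | 1.11 |
| 20% (about 6 of 32) | 4.00 | 5.0 | 1.25 |

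The last row assigns the whole drop-out allowance to this one cause and is an upper illustration.

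**3. When the bias is zero.** If the withdrawn would have averaged the same as the rest of their arm (m = 15), both comparisons give 5.0. If STDP has no effect and the withdrawn show the control change, everyone averages 10 and both comparisons give 0, so the one-sided error stays at 5%.

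**4. What a false-positive problem would need.** Suppose STDP has no effect and both arms average 10 as randomised, but the withdrawn would have averaged m below 10. The completer bias is b = w(10 − m)/(1 − w), with standard error √(36/[32(1 − w)] + 16/32). By normal approximation the one-sided error is 1 − Φ(1.645 − b/SE).

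| Withdrawn | m = 5: bias, error | m = 0: bias, error |
|---|---|---|
| 1 of 32 | 0.16, 6.4% | 0.32, 8.2% |
| 4 of 32 | 0.71, 13.3% | 1.43, 28.2% |

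With a real effect (STDP arm mean 15 as randomised), the bias w(15 − m)/(1 − w) runs from 0.32 (1 of 32, m = 5) to 2.14 (4 of 32, m = 0), against a planned difference of 5. Values of m this low mean that the withdrawn do worse than controls, and nothing in the article indicates that they would.

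**The case against.** The strongest objection lies in the second half of the same sentence. Section 2.1 uses the word follow-up for the scheduled programme out to 12 months, so the promise in section 2.7.2 could mean that these participants keep their visits. The same section also says that judged cardiovascular events are recorded at every visit. On that reading nothing need be lost, MACE included. This stands as a possible reading, but it does not settle the matter. Paired with treatment in a safety section, the phrase reads at least as naturally as care of the event. If it does mean the full schedule with a repeat invasive measurement, it is unclear what being withdrawn from the study means.

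A reader might also infer that the plan builds in a comparison of STDP tolerators with all controls, biased in favour of STDP. The documents do not support that:

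- No section defines a completer analysis or excludes withdrawn participants. The article condenses a full protocol, and leaving analysis sets and missing-data handling to that document or to an analysis plan is no fault.
- The 20% drop-out figure is generic and applies to each arm. It is not tied to adverse-event withdrawals.
- No rate of severe STDP-related events is given, and no link between such events and IMR. The trigger requires both severity and relatedness, so it may be rare.

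These points limit what can be said about size and direction. They do not remove the defect, because the rule about who stays in the study is stated in the text, and an analysis plan cannot supply an IMR that was never measured.

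**Conclusion.** The point holds as a risk, not as an established bias. Section 2.7.2 as written requires study withdrawal on a condition that only the STDP arm can meet, and leaves open whether the 12-month outcomes are still sought. Following it literally could lose the primary endpoint in one arm, possibly informatively.

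The size cannot be fixed from the documents. If the withdrawn show the control change and only completers are compared, the overstatement runs from about 3% (1 of 32) through 11% (10%) to 25% (20%). Under that same assumption there is no bias when STDP has no effect. Larger bias, or inflation of the one-sided error, requires the withdrawn to do worse than controls, which is conceivable but undocumented. With 25 evaluable participants per arm planned, a few such losses could matter.

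**What to change.** Reword the sentence in section 2.7.2 so that stopping STDP and leaving the study are separate events. Leave the clinical decision about the drug as it is. State that participants who stop STDP under this rule stay in scheduled follow-up for MACE and, where consent and condition allow, have IMR, CFR and CTFC measured at 12 months. State that they are analysed in the arm to which they were randomised. If some of these IMR values are still missing, a sensitivity analysis that gives those participants the control-arm change would show how far the result depends on them.

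The cost is one amended sentence and a line on the analysis set, since the visits are already planned. There is a small downside: some 12-month measurements will be taken off drug and may dilute the estimated effect. Under the assumption in step 2, the expected difference would be 4.84 with 1 of 32 withdrawn, or 4.5 at 10%, instead of 5.0, with some loss of power. The change should be made before affected participants reach 12 months, because outcomes not collected then cannot be restored.
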